### Intervention

Basic treatments include metformin, acarbose, insulin, statins, evolocumab, and other standard medical therapies. It is not fixed, individualized plans will be developed by the attending clinicians before the trial, to maintain HbA1c below 8.0% (28) and LDL-C below 1.4 mmol/L (29). Basic treatments will remain unchanged and other TCM therapies are prohibited during the trial.

Participants will take YQYYHX granules or placebo granules for 12 weeks. They should take it 30 min before meals or other medication, at a dose of 12 g per administration, twice daily. The placebo granules contain 10% inert ingredient and 90% excipient (dextrin), with a similar shape, color, and odor as YQYYHX granules.

YQYYHX granules from three different batches were analyzed by Ultra-performance Liquid Chromatography – Mass Spectrometry (Figure 2). Methanol (the extraction solvent) was used as the blank control. The raw data were processed using Progenesis QI 2.4 and subsequently analyzed using a self-built TCM database 2.0 developed by Beijing Junfei Technology Co., Ltd. The top 20 compounds with the largest peak area are shown in Table 2, such as daidzin, salvianolic acid L, and oleamide.

**Figure 2 F2:**
[figure not shown]
Ultra performance liquid chromatography - mass spectrometry of YQYYHX granules. **(A)** Mass spectrogram in positive ion mode. **(B)** Mass spectrogram in negative ion mode. The horizontal axis represents the time points of the reaction, while the vertical axis indicates the sum of the intensities of all ions.

**Table 2 T2:** The 20 compounds with the largest peak area in YQYYHX granules.

Number	Compound	m/z	Retention time (min)	Peak area of batch 1	Peak area of batch 2	Peak area of batch 3	Average peak area of three batches
1	Daidzin	417.12	2.42	53071727.22	52516740.65	55078672.30	53555713.39
2	Salvianolic acid L	717.15	3.30	24740672.84	24566021.34	25515061.76	24940585.31
3	Oleamide	282.28	9.36	31787758.35	16955158.52	14576010.89	21106309.25
4	Nordalbergin	255.07	3.57	18371379.08	18888206.30	19292409.60	18850664.99
5	Prunetin 4'-O-beta-D-glucopyranoside	447.13	2.49	15582195.49	15918850.44	16964987.64	16155344.53
6	Rubiadin primeveroside	549.16	2.37	13864726.60	13906458.78	13672893.43	13814692.94
7	Pulmatin	415.10	2.43	13784453.31	12941732.31	13303108.07	13343097.90
8	Aloe-emodin-8-o-beta-d-glucopyranoside	433.11	2.23	12791583.61	13325067.87	12601173.67	12905941.72
9	Puerarin	417.12	2.62	11951614.58	12073411.38	12506365.38	12177130.45
10	2-Hydroxy-4-allylphenyl 6-O-alpha-L-rhamnopyranosyl-beta-D-glucopyranoside	457.17	3.14	10772289.52	10844833.22	10061076.61	10559399.78
11	3-(1‘,1'-Dimethylallyl)Xanthyletin	297.15	7.06	10267816.25	10780094.15	10611122.83	10553011.08
12	1-Acetoxy-3-methoxy-9,10-anthraquinone	297.08	2.40	11062434.50	9049400.70	9552369.04	9888068.08
13	Lycopic acid C	521.11	3.27	8285120.42	8592400.24	9269637.94	8715719.53
14	L-Arginine	175.12	0.60	8472543.53	7727117.57	7966262.79	8055307.97
15	Isodalbergin	269.08	3.33	7312044.86	7278221.89	7420815.18	7337027.31
16	9S,12S,13S-Trihydroxy-10e-octadecenoic acid	329.23	4.10	7261367.80	7182788.16	6997099.83	7147085.27
17	7-Hydroxy-5,6-dimethoxy-1,4-phenanthrene-quinone	285.08	3.71	6476970.38	6472089.86	6512993.25	6487351.17
18	2-Methyl-N-phenylmaleimide	188.07	2.15	4735472.44	4575310.14	4489001.53	4599928.04
19	Daidzein	253.05	3.58	4469223.58	4534760.76	4669725.29	4557903.21
20	Vitexin	431.10	2.21	4726677.27	4489260.34	4438264.25	4551400.62

### Data management

All observations during the study must be recorded timely, accurately, completely, systematically, and truthfully. The original documents include outpatient medical records, medication administration records, subject diaries, and laboratory or examination reports. Confidential information will be accessible only to investigators and must not be disclosed in any publicly published materials.

Electronic case report forms are generated within the clinical record system, ensuring that all follow-up information is traceable. Baseline data, including sex, age, co-morbidities, concomitant medication, and other relevant characteristics, will also be recorded.

Then it will be entered into a specialized electronic data capture system for this trial. The data administrator will verify the entries and issue queries as needed. When queried, data entry personnel should review the original documents and provide appropriate responses. Then the data administrator will confirm and update the information to ensure consistency between the database and the original records.

### Outcomes

Participants who take the granules for more than 80% of the expected duration will undergo the following assessments before and after the 12-week treatment.

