#### Primary outcome

Brachial–ankle pulse wave velocity (baPWV).

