#### Safety outcomes

Electrocardiogram;

Complete blood count;

Liver and renal function tests;

Urinary albumin-to-creatinine ratio (UACR).

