### Statistical plan

#### Analysis sets

The full analysis set (FAS) includes all participants who were randomized, using their last observed data as the trial outcome for intention-to-treat analysis. The per-protocol set (PPS) refers to participants who strictly adhered to the trial protocol, demonstrated good compliance, did not take prohibited medications during the trial, and completed the required case report forms. It will be utilized for the primary efficacy analysis. The safety set (SS) comprises all participants who were randomized, received at least one dose of the study treatment, and have post-treatment safety data available. Statistical descriptions and analyses of their safety outcomes and adverse event incidence will be performed.

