### Conditions for suspension, drop-out and termination

In accordance with medical standards, participant safety considerations, and GCP requirements, investigators will determine whether a participant needs to suspend or drop-out. Participants will be classified as drop-out if they are newly diagnosed with other diseases that may influence the trial, if they begin using other traditional Chinese medicines with similar therapeutic effects, or if they are lost to follow-up during the observation period.

An adverse event refers to any unfavorable medical occurrence during the study, regardless of whether it is causally related to the intervention. It includes clinically significant abnormalities in electrocardiogram, liver function, or renal function tests, as well as any subjective symptoms of discomfort reported by the participants. If it occurs, investigators should record, assess the severity and the relationship with the trial, and observe until returning to normal. A serious adverse event is any unfavorable medical occurrence that result in hospitalization, disability, incapacity, or even life-threatening conditions. It requires immediate medical management plus immediate reporting to the principal investigator once known, followed by expedited reporting to the ethics committee. If more than half of the participants experience serious adverse events, the trial must be terminated.

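### As worded, the Outcomes section reserves the scheduled efficacy and safety assessments for participants above 80% adherence, which conflicts with the all-randomised full analysis set and the one-dose safety set

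*Protocol article*

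**What the plan says.** Under Outcomes, one sentence governs everything listed after it: "Participants who take the granules for more than 80% of the expected duration will undergo the following assessments before and after the 12-week treatment". The list begins with "Brachial–ankle pulse wave velocity (baPWV)" as primary outcome and continues with the secondary outcomes. It then gives the safety outcomes: electrocardiogram, blood count, "Liver and renal function tests", and UACR.

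Under Analysis sets:

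- **Full analysis set (FAS):** "The full analysis set (FAS) includes all participants who were randomized, using their last observed data as the trial outcome for intention-to-treat analysis".
- **Per-protocol set (PPS):** "participants who strictly adhered to the trial protocol, demonstrated good compliance, did not take prohibited medications during the trial", with completed case report forms. Of this set the article says "It will be utilized for the primary efficacy analysis". The definition gives no adherence percentage.
- **Safety set:** randomised, dosed at least once, and with safety data after treatment.

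Under Multiple imputation, missing outcomes are imputed assuming missing at random.

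Under Conditions for suspension, drop-out and termination, "Participants will be classified as drop-out if they are newly diagnosed with other diseases that may influence the trial". Starting a similar traditional medicine or being lost to follow-up also counts. That section does not say whether a drop-out is still assessed at week 12. It defines adverse events without any adherence condition, and includes clinically significant ECG, liver and renal abnormalities.

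**The concern.** Adherence arises after randomisation, and treatment can influence it through tolerability, taste or perceived benefit. If it decides who is measured at week 12, the two measured groups are no longer the two randomised groups. An analysis plan cannot repair this later, because the outcomes were never collected.

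Three things are at stake:

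- **Efficacy.** The FAS should show whether a result in compliant participants survives when everyone is counted. It cannot do so without week-12 values from non-adherers.
- **Safety.** A silent change in liver enzymes, creatinine or ECG is found only by testing. A participant who stopped because of intolerance is one whom the scheduled tests should reach.
- **Timing.** Under Trial status, 72 participants were enrolled and 38 had completed observation by 10 March 2026. A missed week-12 measurement cannot be recovered.

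**Working it through.** **1. The plan's own figure.** Inputs from Sample size: means 1600 and 1440 cm/s (difference 160), SDs 260 and 234, two-sided α = 0.05, power 0.90. The normal formula gives n = (1.960 + 1.282)² × (260² + 234²) / 160² = 10.507 × 122,356 / 25,600 = 50.2, so 51 per group. The unequal-variance t-test gives power 0.899 at 51 and 0.904 at 52, so the stated 52 is reproduced. Dividing by one minus the dropout rate gives 52/0.90 = 57.8 (58) and 52/0.85 = 61.2 (62). The stated 60 lies between. The sample size is not in dispute.

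**2. The sections side by side, for a participant at or below 80%.**

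| Section | Literal consequence |
|---|---|
| Outcomes | No week-12 baPWV, secondary outcomes or scheduled safety tests |
| FAS | Included, but with assessments only before and after treatment the last value is baseline |
| Multiple imputation | No observed week-12 values off treatment, so the model borrows from adherers |
| Safety set | Can be excluded for want of safety data after treatment |
| PPS (primary for efficacy) | Excluded if compliance is judged not good |
| Adverse events | Still recorded |

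The rule does not reach everyone who stops early. Since 80% of 84 days is 67.2 days, a participant who stops from about day 68 is still assessed.

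**3. Illustration for an assessed-only or per-protocol comparison.** If a fraction q of one arm is unmeasured and its mean is D higher than that of the measured remainder, the measured mean is too low by q × D. Assume q = 0.15 in the active arm, D = 130 cm/s (half of the SD of 260), and random non-assessment on placebo. None of these assumptions is in the article.

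- Bias = 0.15 × 130 = 19.5 cm/s in favour of YQYYHX.
- 19.5/160 = 12% of the planned difference.
- 19.5/100 = about 20% of the minimal clinically important difference that the article cites.

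**4. Range under a second model.** Assume no true effect, 54 placebo participants measured (10% lost at random), and the worst-prognosis fraction q of the active arm unmeasured. Assume also a correlation ρ of 0.2 to 0.5 between that prognosis and baPWV, and SD √(122,356/2) = 247. Bias = ρ × 247 × φ(z)/(1 − q), where z is the 1 − q normal quantile. At q = 0.15, φ(z) = 0.233 and φ(z)/(1 − q) = 0.274, which gives 14 cm/s (ρ = 0.2) to 34 cm/s (ρ = 0.5).

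| Unassessed, active arm | Spurious benefit (cm/s) | Type I error (nominal 5%) |
|---|---|---|
| 10% | 10–24 | 5.5–8.0% |
| 15% | 14–34 | 5.9–10.8% |
| 20% | 17–43 | 6.4–14.3% |
| 25% | 21–52 | 7.0–18.3% |

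**5. The FAS behaves differently.** Carrying baseline forward returns the unassessed participants with their own starting value. Take a baseline of 1600 cm/s, an unchanged control arm and 15% of the active arm carried forward. The expected difference is then 0.85 × 160 = 136 cm/s.

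- If those participants truly gained the full 160, the FAS understates the effect by 24 cm/s.
- If they gained nothing, it is unbiased.
- If they worsened beyond baseline, it favours YQYYHX.

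The direction is therefore not fixed.

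**The case against.** The strongest reply is that the sentence does not mean what it says. Adherence cannot be a condition for tests done before the first dose. A one-dose safety set would have little purpose if only those above 80% were tested. The visit schedule (Table 1) is not shown and may apply to everyone. This stands as a reason for caution: what can be shown is a conflict in the text, not that assessments are being withheld. It does not remove the point. The sentence sits under Outcomes and states who is assessed, the PPS definition does not use the figure, and no other section shown provides a week-12 assessment for the remaining participants. If a compliance criterion was meant, the correction is the same.

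A reader might go further and infer four things that the article does not support:

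- **That safety data as a whole are selected, or that harm is hidden.** Adverse event recording is unrestricted, so only the scheduled tests are affected.
- **That every analysis set is biased towards YQYYHX.** Step 5 shows that the FAS can move either way. Baseline-adjusted ANCOVA, which Outcome analysis allows, would also absorb part of any difference already present at baseline.
- **That 10–15% of 120, or 12 to 18 people, would lack safety tests because of this rule.** The dropout allowance is not a non-adherence rate. It includes loss to follow-up, which no assessment rule can cure.
- **That all drop-outs go unassessed.** The section that defines drop-out does not say so.

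**Conclusion.** The point holds as an internal conflict with practical consequences if the sentence is followed. The Outcomes section limits scheduled assessment by adherence, while Analysis sets relies on outcomes from all randomised participants and on safety data from anyone dosed. Confidence in the conflict is high. Confidence that staff actually omit the visits is only moderate, because Table 1 is not visible.

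The article gives no adherence pattern from which to size the bias. The figure of about 20 cm/s rests wholly on the assumed 15%, 130 cm/s and one-sided selection, and it applies to an assessed-only or per-protocol comparison. Under the second model, 10–25% unassessed gives 10–52 cm/s, at most about half of 100 cm/s.

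Correcting the Outcomes sentence alone would not protect the headline result. The PPS is named for the primary efficacy analysis and selects on compliance again.

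**What to change.** 1. In Outcomes, replace the opening sentence with, for example: *Every randomised participant is assessed at baseline and at week 12 on all outcomes listed below, whether or not the granules were taken as planned or stopped early.*
2. Use the 80% threshold only in the PPS definition.
3. In Analysis sets, make the FAS the set for the primary efficacy analysis, with the PPS as a sensitivity analysis.
4. Check that Table 1 agrees.
5. Apply the change to enrolled participants who have not yet reached week 12 as well as to new ones. On the March 2026 counts this is at most 120 − 38 = 82 people: 72 − 38 = 34 enrolled but not recorded as complete, and 120 − 72 = 48 still to enrol.

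**Cost.** A protocol amendment and some week-12 visits for participants who have stopped the granules. No new time point is needed and N stays at 60 per group. With all 60 per group measured, planning power is 0.94 if the full 160 cm/s applies to everyone. If 15% of the active arm gained nothing, the difference would be 136 cm/s and power about 0.85 with the SDs unchanged (t-test with 60 per group; 136/√(122,356/60) = 136/45.2 = 3.01). That is somewhat below the planned 0.90. The loss reflects what happens in the randomised population.

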#### Primary outcome

Brachial–ankle pulse wave velocity (baPWV).

#### Secondary outcomes

Ankle–Brachial Index (ABI);

Fasting BG and HbA1c;

Lipid profiles;

Inflammatory cytokines;

6-min walk test;

Vascular Quality of Life Questionnaire-6 (VascuQol-6), symptom questionnaire, and TCM syndrome questionnaire (Tables S1–S3).

#### Safety outcomes

Electrocardiogram;

Complete blood count;

Liver and renal function tests;

Urinary albumin-to-creatinine ratio (UACR).

#### Exploratory mechanistic analysis

Serum and fecal samples from participants will be collected and stored at −80°C. After unblinding, serum samples from 30 participants in the treatment group will be used for metabolomic and proteomic sequencing, as well as other related analysis, while fecal samples will be used for metagenomic sequencing analysis. This study commits to handling all biological samples in strict accordance with regulatory requirements, ensuring that samples are not used for any unauthorized or unlawful research. All samples will be promptly destroyed after completion of the planned analyses.

Raw data will undergo quality control and appropriate preprocessing, followed by analysis using suitable statistical models, with multiple testing controlled by the Benjamini-Hochberg method. The identified molecular features will be further subjected to functional interpretation and exploratory integration with the clinical outcomes.

### Statistical plan

#### Analysis sets

The full analysis set (FAS) includes all participants who were randomized, using their last observed data as the trial outcome for intention-to-treat analysis. The per-protocol set (PPS) refers to participants who strictly adhered to the trial protocol, demonstrated good compliance, did not take prohibited medications during the trial, and completed the required case report forms. It will be utilized for the primary efficacy analysis. The safety set (SS) comprises all participants who were randomized, received at least one dose of the study treatment, and have post-treatment safety data available. Statistical descriptions and analyses of their safety outcomes and adverse event incidence will be performed.

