### Sample size

The mean ± SD of baPWV among T2DM patients was 1548.87 ± 305.48 cm/s in Beijing, China (aged 20–80 years) (21), 1580 ± 324 cm/s in Nanchang, China (aged 17–75 years) (22), and 1534.2 ± 254 cm/s in Kagoshima, Japan (aged 22–84 years) (23). Among healthy people, it was 1200 ± 150 cm/s (aged 40–49 years), 1390 ± 190 cm/s (aged 50–59 years), 1630 ± 300 cm/s (aged > 60 years) in Xinjiang, China (24).

Considering that the above data were derived from small-sample studies and the age ranges were not consistent with this study, we hypothesized that the baPWV was 1600 ± 260 cm/s for T2DM patients aged 40–85 years, and YQYYHX was expected to reduce it to 1440 ± 234 cm/s (25, 26). A change of 100 cm/s may represent a minimal clinically important difference (27). This study is designed by superiority, and the ratio between the treatment and control groups is 1:1. With a two-sided α = 0.05 and β = 0.1, the sample size is calculated to be 52 in each group using a *t*-test allowing unequal variances in PASS 15. The formula is as follows.

$$\begin{array}{l} n=\frac{{\left(Z_{1-\alpha /2}\;+\;Z_{1-\beta }\right)}^{2}\cdot 2\sigma^{2}}{{\left(\mu_{1}-\mu_{2}\right)}^{2}} \end{array}$$

Considering a 10%−15% dropout rate, 60 patients are needed in each group and the total sample size is 120.

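### The per-protocol set is the primary efficacy population of a superiority trial, so the baPWV comparison loses the protection of randomisation and its 0.05 error rate is not assured

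*Protocol article*

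**What the plan says.** Three analysis sets are defined under Analysis sets. The FAS "includes all participants who were randomized, using their last observed data as the trial outcome for intention-to-treat analysis". The PPS consists of "participants who strictly adhered to the trial protocol, demonstrated good compliance, did not take prohibited medications during the trial", and who also have complete case report forms. The sentence straight after the PPS definition reads "It will be utilized for the primary efficacy analysis"; its subject can only be the PPS. No other section makes the FAS primary or co-primary. Outcome analysis mentions a sensitivity analysis for protocol deviations without naming a population.

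The Sample size section states the objective: "This study is designed by superiority, and the ratio between the treatment and control groups is 1:1".

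Three other sections bear on the point:

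- **Outcomes** limits the before-and-after assessments to participants who took the granules for more than 80% of the planned duration.
- **Interim analysis** sets an overall two-sided type I error of 0.05 and allows an early efficacy stop on baPWV. It does not name an analysis set.
- **Multiple imputation** plans imputation under missing at random, alongside the last-observation rule written into the FAS.

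**The concern.** Every condition for entering the PPS is met or failed after allocation. Adherence, use of prohibited medication and completion of records can all depend on tolerability or perceived benefit, and these can differ between an active granule and a placebo. The drop-out grounds the protocol lists (new disease, starting a similar traditional medicine, loss to follow-up) are open to the same influence. Once such participants are removed, the arms are no longer comparable by design.

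In a superiority trial the usual risk is that participants who do poorly leave the active arm and the remainder look better than the arm as a whole. An alpha-spending boundary controls the error from repeated looks; it does nothing about selection. At stake is the headline baPWV result and, if the interim look also uses the PPS, a recommendation to stop early.

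**Working it through.** **1. The plan's own sample size.** Inputs from the Sample size section: means 1600 and 1440 cm/s (difference 160), SDs 260 and 234, two-sided α 0.05, power 0.90.

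- Normal approximation: n = (1.96 + 1.2816)² × (260² + 234²) / 160² = 50.2, so 51 per arm.
- Unequal-variance t-test (noncentral t): 51 per arm gives 89.9% and 52 gives 90.4%. The stated 52 is reproduced.
- 60 per arm leaves 52 after a loss of 1 − 52/60 = 13.3%, within the stated 10–15%.

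The sample size is not at fault.

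**2. False-positive rate under a simple assumed selection.** Suppose there is no true effect and 15% of each arm is excluded, leaving 60 × 0.85 = 51. Placebo exclusions are random. Those excluded from the active arm have baPWV 130 cm/s higher than those retained. The 130 cm/s and the one-sided pattern are assumptions.

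- SE = √((260² + 234²)/51) = 49.0 cm/s
- Spurious benefit = 0.15 × 130 = 19.5 cm/s, or 19.5/49.0 = 0.398 SE
- False result favouring YQYYHX: 1 − Φ(1.96 − 0.398) = 5.9%, against 2.5% nominal
- False result in the other direction: Φ(−1.96 − 0.398) = 0.9%
- Two-sided error = 5.9% + 0.9% = 6.8%, against 5%

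Stronger assumed selection, same formula:

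| Assumption (active arm) | n per arm | Bias (cm/s) | Shift (SE) | Favouring YQYYHX | Two-sided |
|---|---|---|---|---|---|
| 15% excluded, 130 cm/s higher | 51 | 19.5 | 0.398 | 5.9% | 6.8% |
| 15% excluded, 200 cm/s higher | 51 | 30 | 0.612 | 8.9% | 9.4% |
| 30% excluded, 130 cm/s higher | 42 | 39 | 0.723 | 10.8% | 11.2% |

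The last row uses twice the protocol's upper dropout figure. PPS exclusions can exceed dropout, but nothing in the protocol says they will.

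**3. A second method.** Simulation under no effect: 60 per arm, common SD 247 (the mean of 260 and 234), Welch test at two-sided 0.05, 40,000 runs. Exclusion follows a latent variable with correlation ρ to the outcome, so participants with high baPWV are more likely to be excluded.

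| Excluded, active vs placebo | ρ = 0 | ρ = 0.3 | ρ = 0.5 | ρ = 1 (extreme) |
|---|---|---|---|---|
| 13.3% vs 13.3% | 0.049 | 0.051 | 0.048 | 0.049 |
| 15% vs 5% | 0.049 | 0.056 | 0.073 | 0.166 |
| 20% vs 5% | 0.049 | 0.065 | 0.095 | 0.309 |

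For 15% vs 5%, the spurious benefit is about 12, 20 and 41 cm/s at ρ = 0.3, 0.5 and 1. With no correlation, or with equal exclusion and the same selection in both arms, the error stays at about 0.05. Steps 2 and 3 treat the analysis as a single look.

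**4. Power if all randomised participants are analysed.** With 60 per arm and the full 160 cm/s, power is 94.0%. If those who would have been excluded gain no benefit (an assumption, SDs unchanged):

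| Otherwise excluded | Diluted effect (cm/s) | Power, all 60 per arm | Power, PPS with the full 160 cm/s |
|---|---|---|---|
| 10% | 160 × 0.90 = 144 | 88.5% | 91.5% (54 per arm) |
| 13.3% | 160 × 0.867 = 138.7 | 86.1% | 90.4% (52 per arm) |
| 15% | 160 × 0.85 = 136 | 84.8% | 89.9% (51 per arm) |

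**The case against.** The best defence has three parts.

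**Blinding.** Participants and investigators are blinded and the placebo is matched in shape, colour and odour, so exclusions may well be similar in the two arms. In that case the simulation shows no inflation. This stands as a reason for doubting that the bias is large. It does not remove the problem, because tolerability and perceived lack of benefit can differ by arm under perfect blinding.

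**Direction.** The calculation in step 2 puts all the outcome-related exclusion in the active arm. If it fell mainly on placebo, the bias would run against YQYYHX. This also stands: neither sign nor size is known.

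**Intention-to-treat is planned.** The FAS exists and assigned arms are kept, so it would be too strong to say that randomisation is discarded. The fault is which set carries the primary claim.

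Two stronger readings are tempting and are not supported. A reader might infer that the true type I error must exceed 0.05; the protocol has no exclusion rates by arm and no outcome data on those excluded, so it shows only that 0.05 is not guaranteed. A reader might also infer that the interim boundary is to be applied to the PPS. The Interim analysis section names no set. The PPS is the only set given to primary efficacy, which makes that a natural reading, but it remains an inference.

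**Conclusion.** The point holds and should be corrected before any unblinded look. The choice of the PPS is explicit, so it is not a detail left to an analysis plan, and it is the wrong primary population for a superiority claim. The consequence is conditional: two-sided error remains about 5% when exclusion is unrelated to outcome or selects equally in both arms, rises to about 6.8% under the moderate one-sided scenario in step 2, and goes higher with stronger or more unequal selection. All figures above 5% rest on assumed exclusion rates and outcome differences. If the interim efficacy look uses the PPS, it has the same weakness.

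**What to change.** Three linked changes are needed, because renaming the primary set alone would leave non-adherers without a week-12 value.

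1. **Analysis sets and Interim analysis:** state that the primary efficacy analysis, at the interim and at the end, includes all randomised participants in the arm to which they were allocated, whatever their adherence or concomitant medication. Make the PPS supportive, with no part in the efficacy decision.
2. **Outcomes:** remove the 80% condition for outcome assessment, so that week-12 baPWV is sought from every randomised participant.
3. **Missing values:** reconcile the FAS last-observation rule with the Multiple imputation section, and use multiple imputation for missing week-12 baPWV in the primary analysis. Because outcomes are assessed only before and after treatment, a non-completer's last observed value may simply be the baseline.

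**Cost.** No increase in the planned 120 is needed. The estimate may be somewhat smaller, with the power shown in step 4, and follow-up of non-adherers takes some extra effort. On 10 March 2026, 72 participants were enrolled and 38 had completed observation. That is 38/120 = 32% of the planned total, short of the 50% information point, so at that date the change would still have preceded the interim look. Some week-12 values may already be uncollected among those enrolled; these should be counted and reported by arm.

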#### Multiple imputation

If any outcomes are randomly missing, multiple imputation will be used to enhance statistical power. Assuming that the missing data follow the Missing at Random assumption, the analysis results from multiple imputed datasets will be combined using Rubin's Rules. Methods such as comparison of distribution similarity, regression results, and Monte Carlo error assessment will be used to ensure the quality of imputation.

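### The primary efficacy analysis of a superiority trial is assigned to the per-protocol set, so the primary comparison does not keep the randomized groups intact

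*Protocol article*

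**What the plan says.** The Sample size section sets the objective: "This study is designed by superiority", with 1:1 allocation and a two-sided α of 0.05.

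Analysis sets defines two efficacy sets. The full analysis set (FAS) holds everyone randomized, "using their last observed data as the trial outcome for intention-to-treat analysis". The PPS holds "participants who strictly adhered to the trial protocol, demonstrated good compliance", with the further conditions of no prohibited medication and completed case report forms. The sentence that follows the PPS definition reads "It will be utilized for the primary efficacy analysis". Its subject is the PPS. No other text gives the FAS primary or co-primary status.

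Three other statements bear on the point:

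- Intervention: "Basic treatments will remain unchanged and other TCM therapies are prohibited during the trial". No exception for a medically needed change is given.
- Outcomes: "Participants who take the granules for more than 80% of the expected duration will undergo the following assessments" before and after the 12 weeks.
- Multiple imputation: "If any outcomes are randomly missing, multiple imputation will be used", under a missing-at-random assumption.

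**The concern.** Randomization protects a superiority comparison only while the analysed groups are the randomized groups. Each PPS condition is judged after treatment has started and may be affected by treatment, by prognosis, or by both. If exclusions differ between arms in a way related to baPWV, the primary estimate mixes the treatment effect with a selection effect, and no later adjustment reliably separates them.

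A change in background treatment shows how this could happen. The individualized plans aim at HbA1c below 8.0% and LDL-C below 1.4 mmol/L, and are then meant to stay fixed. A participant who loses control may need a change, and a strict reader could call that a departure from the protocol. The trigger is something on which the granules are being tested: "Fasting BG and HbA1c" and the lipid profile are secondary outcomes. The Discussion also links HbA1c and some lipid measures to arterial stiffness. Exclusion could therefore depend on both treatment and outcome.

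**Working it through.** **1. The plan's own sample size.** Inputs from Sample size: means 1600 and 1440 cm/s, SDs 260 and 234, two-sided α 0.05, power 0.90. For n per arm, SE = √(260²/n + 234²/n). Power of the unequal-variance t-test comes from the noncentral t distribution.

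- n = 51: SE 49.0, power 0.899.
- n = 52: SE 48.5, power 0.904. The stated 52 reproduces.
- n = 54: power 0.915.
- n = 60: power 0.940, if the design effect holds in everyone randomized.

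The sample size is not in dispute, and the proposed change leaves it as it is.

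**2. Which set is primary.** The text gives superiority as the objective, the PPS as the primary efficacy set, and the FAS without primary status. This step needs no arithmetic and is the whole of the documented defect.

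**3. An illustration of size.** The document gives neither exclusion rates nor a correlation, so the following are assumptions: 60 per arm; correlation ρ of 0.1 to 0.3 between glucose or lipid control and baPWV; removal of exactly the worst-controlled fraction q of an arm, which is the largest effect for that q and ρ; a single-look test.

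Removing the upper fraction q lowers an arm's mean baPWV by ρ × SD × φ(z₁₋q)/(1 − q). The factor φ(z₁₋q)/(1 − q) is 0.109 at q = 0.05, 0.195 at 0.10 and 0.274 at 0.15. Net shift = placebo shift (SD 260) minus YQYYHX shift (SD 234):

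| Removed, placebo / YQYYHX | ρ = 0.1 | ρ = 0.3 | Effect on estimated benefit |
|---|---|---|---|
| 10% / 10% | 0.5 cm/s | 1.5 cm/s | negligible |
| 15% / 5% | 4.6 cm/s | 13.8 cm/s | understated |
| 5% / 15% | 3.6 cm/s | 10.8 cm/s | overstated |

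Example, second row at ρ = 0.1: 0.1 × 260 × 0.274 = 7.1; 0.1 × 234 × 0.109 = 2.5; difference 4.6.

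Against the standard error:

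- 15% / 5% leaves 51 placebo and 57 YQYYHX, SE 47.8. The shift is 0.10 to 0.29 SE, and power at 160 cm/s falls from 0.91 to 0.90–0.86.
- 5% / 15% leaves 57 and 51, SE 47.5. The shift is 0.08 to 0.23 SE.

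**4. Type I error.** Simulation with no true effect, SD 260 in both arms, 60 per arm, and 3 placebo and 9 YQYYHX participants removed from the worst tail:

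- ρ = 0.1: mean shift about 4 cm/s, two-sided rejection 0.051.
- ρ = 0.3: mean shift about 13 cm/s, two-sided rejection 0.059 to 0.060.

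Rejections in favour of YQYYHX alone rise from 0.025 to 0.030 and about 0.045. That is the one-sided view; the trial is two-sided. With equal removal in both arms the bias is about zero and the two-sided error stays near 0.05. The result depends on ρ: an assumed 0.5 would give about 22 cm/s and 0.07 to 0.08.

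**The case against.** The strongest reply is that the background-treatment route is not in the document. Analysis sets names prohibited medication, and the only therapies that Intervention calls prohibited are other TCM therapies. The section on suspension, drop-out and termination lists new disease, similar TCM use and loss to follow-up, but no change in background treatment. A reader might infer that the plan excludes participants whose glucose- or lipid-lowering treatment changes. It does not say so, and detailed PPS rules may sit in an analysis plan that is not shown. This part of the objection stands: the route is only an example. A stable-background rule is also ordinary and is not an error in itself.

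The size may well be small. Plans are set before the trial, treatment lasts 12 weeks, and nothing supports 5% to 15% of participants needing a change. The lipid link is loose: the target is LDL-C, while the Discussion relates baPWV or stiffness to triglycerides, lipid accumulation products and the triglyceride-glucose index. A reader might also infer a bias in favour of YQYYHX. By this route that would need worse control under YQYYHX than under placebo; if the granules improve control, the benefit is understated. The document does not settle the direction.

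A third tempting inference is that the PPS leaves no margin in sample size: 60 × 0.90 = 54 and 60 × 0.85 = 51, against 52 required. Some drop-out grounds are also PPS exclusions, so subtracting both counts some participants twice. Power is not the argument here.

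Finally, an intention-to-treat analysis and a sensitivity analysis for protocol deviations are planned, so readers would see other results. That helps interpretation but does not change which result decides the trial. Double blinding reduces unequal exclusion but cannot remove it where the need for a change follows from the treatment itself.

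**Conclusion.** The point holds as a matter of the primary analysis set. The article states a superiority objective and gives the primary efficacy analysis to a set chosen after randomization. That follows from the text and needs none of the assumed figures.

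The size and direction of any bias are unknown. For the one illustrated route, unequal removal of the worst tail (5% against 15%) with a correlation of 0.1 to 0.3 gives a shift of about 4 to 14 cm/s and a two-sided type I error of about 0.05 to 0.06. Against the article's minimal important difference of 100 cm/s and design effect of 160 cm/s, this is modest. Equal removal does almost nothing. The change should be made because it removes an avoidable source of bias at little cost; a large distortion has not been shown.

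**What to change.** - Make the primary baPWV analysis include all randomized participants in their assigned arms, with the PPS analysis as supportive.
- Carry out week-12 assessments in everyone, whatever their intake relative to the 80% condition in Outcomes and whatever changes in background treatment occurred. Without this, the all-randomized set may lack the data it needs.
- For missing week-12 baPWV in this set, use the multiple imputation already planned in place of last observed data. Where no later value exists, the last observed value is the baseline.
- State that a medically required change in background treatment is not a ground for exclusion from this analysis.

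Make the change while the trial is blinded and, if possible, before the interim analysis at about 50% information, which can lead to a recommendation to stop early. Trial status reports 38 completers on March 10, 2026.

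The cost is a few sentences and the effort of assessing participants who stop the granules. Including non-adherers may dilute the estimated effect slightly; the supportive PPS analysis will help show by how much.
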